**Recruitment:** During study hours (we anticipate that this will be 5 to 10 PM, 7 days a week, but this may increase or decrease weekly as resources dictate), ED study staff will routinely offer a universal voluntary mental health screen to all medically stable adolescents aged 12-17 presenting with a custodial parent/guardian and with non-psychiatric complaints to the ED. Adolescents who screen positive on the ASQ and meet inclusion/exclusion criteria will be offered enrollment into the randomized control trial by trained research coordinators. In addition, all subjects at flight risk or imminent suicide risk will be treated as per the ED flight risk protocol. Subjects and families will be recruited according to IRB and Office for Human Research Protection (OHRP) guidelines. No research procedures will be performed prior to informed consent. After enrollment but prior to randomization, the Clinical Research Coordinator will give a brief description of the problems endorsed to the parent and adolescent and then conduct the baseline assessments. Once baseline surveys are complete, randomization will occur into either Enhanced Usual Care (EUC) or the STAT-ED intervention. If randomized into EUC, the adolescent will receive a psychiatric evaluation and a mental health referral from the ED psychiatric social worker. Because this is a study of high risk children, all adolescents in EUC will be evaluated by the ED psychiatric social worker as per their usual suicide risk assessment and be offered a referral, if clinically indicated. If randomized into the STAT-ED intervention, the adolescent and parent will receive a brief motivational interview, barrier reduction discussion, and referral and limited case management by the study social worker to enhance outpatient mental health follow up after discharge from the ED. This will include phone follow up to facilitate referrals, answer questions, help with barrier and logistical issues, until the first mental health follow up visit appointment date. Because by definition all adolescents in the study will be at risk for suicide, each will receive a full risk assessment while in the ED (by the study social worker in the intervention group or by the ED psychiatric social worker if in the EUC group). Study social workers will be trained to give full assessment of all suicidal patients as per the Psych ED suicide assessment protocol. These protocols (STAT-ED and EUC) were followed during the pilot study without complication. Adolescents thought to be at too high of risk to send home will be admitted and will continue to be followed in the study. No pilot study patients were severe enough to be admitted during the pilot study.

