
**Method for Randomization:** Participants will be randomized into the EUC or STAT-ED arm in computer generated blocks of 10 to the intervention and control groups. A computerized random number generator will be used to derive a list for randomization. Research staff performing follow up telephone surveys and data analysts will be blind to the participant's group allocation. A data analyst separate from the study statistician will generate a random sequence of numbers to be printed and placed in radio-opaque

envelopes with a sticker seal indicating the block in which the envelope is to be placed. Upon consent, the research social worker will take the next envelope, break the seal and determine whether the adolescent will receive the STAT-ED intervention or EUC thereby assuring allocation concealment.

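### The envelope is opened at consent in one place while randomisation follows baseline elsewhere; separately, a labelled fixed block of 10 makes the concealment claim too strong

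*Protocol*

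**What the plan says.** **Timing.** Under Method for Randomization (PROCEDURE), the protocol instructs: "Upon consent, the research social worker will take the next envelope, break the seal". Under Recruitment, in the same section, it says: "Once baseline surveys are complete, randomization will occur into either Enhanced Usual Care (EUC) or the STAT-ED intervention". Recruitment also places the baseline work before allocation: "After enrollment but prior to randomization, the Clinical Research Coordinator will give a brief description of the problems endorsed", followed by the baseline assessments. Study Design and the opening paragraph of PROCEDURE both list initial assessment as step 2 and randomisation as step 3.

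**Blocks and envelopes.** Method for Randomization states: "Participants will be randomized into the EUC or STAT-ED arm in computer generated blocks of 10". The slips go into radio-opaque "envelopes with a sticker seal indicating the block in which the envelope is to be placed". The research social worker opens the envelope to "determine whether the adolescent will receive the STAT-ED intervention or EUC thereby assuring allocation concealment".

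**Roles.** Recruitment says that eligible adolescents "will be offered enrollment into the randomized control trial by trained research coordinators", and gives the baseline assessments to the Clinical Research Coordinator. A data analyst separate from the study statistician generates the sequence. Follow-up telephone staff and data analysts are to be blind to allocation.

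**The concern.** There are two separate problems.

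First, the protocol gives two different moments for revealing the arm. If sites follow the envelope instruction, the arm is known in the ED before the baseline measures are taken. The hypotheses under PURPOSE imply that these cover suicidal ideation, depression, barriers to treatment and stage of change. Families who leave between consent and baseline would already be randomised. Because Sample Size Justification commits to an intention-to-treat analysis that keeps all 160 subjects, they would enter the analysis without baseline data.

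Second, an opaque envelope hides its own slip but not what can be deduced from slips already opened. When the block size is known and the block is marked on the seal, the end of each block can be worked out by someone who has seen its earlier allocations. The statement that the procedure assures concealment does not allow for this.

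**Working it through.** **1. Timing: the statements side by side**

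- Study Design and the start of PROCEDURE: recruit, assess, randomise, follow up, in that order.
- Recruitment: no research procedure before consent; baseline after enrolment and before randomisation; randomisation once the baseline surveys are done.
- Method for Randomization: envelope opened and arm determined at consent.

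Consent must come before baseline, and by the first two items baseline must come before randomisation. Consent and randomisation are therefore separated by the whole baseline assessment, and the third item cannot be reconciled with the others as worded. Nothing in the protocol says which statement governs.

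**2. Predictability within a block**

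The protocol gives no figure here, so there is none to reproduce. Inputs and assumptions:

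- Block size 2m = 10, so m = 5 (Method for Randomization).
- 5:5 within each block. This is inferred from 80 per arm; it is not stated.
- 160 participants, 80 per site (Study Sample), giving 160/10 = 16 blocks.
- Assumed: each block is used up at one site, and the opener knows the block size, the block boundary and every earlier allocation in the block.

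*Allocations known with certainty.* Once one arm's five places are used, the rest of the block is fixed. The expected length of that tail is 2m/(m + 1) = 10/6 = 1.67, or 16.7% of the block. Over 16 blocks: 16 × 1.667 = 26.7, about 27 of 160 (about 13 of 80 per site).

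Enumerating all C(10,5) = 252 orderings gives this distribution of the tail length:

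| Length of known tail | Share of blocks |
|---|---|
| 1 | 55.6% |
| 2 | 27.8% |
| 3 | 11.9% |
| 4 | 4.0% |
| 5 | 0.8% |

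The last allocation is always known, and at least the last two are known in 100% − 55.6% = 44.4% of blocks.

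*Best guess.* Always guess the arm with fewer allocations so far. Expected correct guesses per block are m + 2^(2m−1)/C(2m,m) − 1/2 = 5 + 512/252 − 0.5 = 6.53 of 10, or 65.3%, against 50% under simple randomisation. Over 160 this is 0.653 × 160, about 105 against 80.

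**3. Would varying the block size help?**

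The same formula gives 2.833, 4.100, 5.329 and 6.532 correct guesses for blocks of 4, 6, 8 and 10. For equal mixes:

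- 4/6/8: (2.833 + 4.100 + 5.329)/18 = 12.262/18 = 68.1%
- 6/8/10: (4.100 + 5.329 + 6.532)/24 = 15.961/24 = 66.5%

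Simulated lists of 80 gave 67.9% and 66.1%. The guessing rule needs only the running difference between arms, not the block boundaries, so hiding the sizes does not defeat it. Varied, undisclosed sizes do remove the certainty that comes from a known block end, but the guess rate does not fall below the 65% of fixed blocks of 10.

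**The case against.** The strongest reply is that the intended order is plain. Three places put baseline first, and the words about consent may be loose shorthand for a family that has consented and been assessed. That is a likely reading of the intention. It does not remove the contradiction, because the sentence in question is the operating instruction for the envelope and two sites have to follow it.

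A reader might infer more than the protocol supports, in four ways.

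- *That baseline scores or enrolment will be biased.* The social worker opens the envelope; coordinators offer enrolment and conduct baseline. Bias needs the arm, or the likely next arm, to be passed on. The protocol has no rule against this and does not say whether the envelope opener also delivers STAT-ED, but the path is possible rather than shown.
- *That one person sees every allocation.* The protocol does not say so. There are two sites, recruitment is planned seven days a week, and study social workers appear in the plural. Whether blocks are kept by site is not stated; shared blocks would lower predictability at each site.
- *That the outcome used for sample size is compromised.* Treatment initiation within two months is verified with the provider and assessed by blinded staff, and it has no baseline score. The exposure is mainly baseline ideation and depression, and the barrier and stage-of-change measures, which serve exploratory aims. Age, gender and ethnicity cannot be coloured by knowing the arm. Baseline covariates enter the models only if imbalance is found.
- *That many families would be lost between consent and baseline.* Consent, baseline and randomisation appear to fall within one ED visit, so the interval is probably short.

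These limits reduce the likely harm. They do not touch the contradiction or the overstated concealment claim.

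**Conclusion.** The point stands in two parts.

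The timing contradiction is certain on the text. Its consequences are conditional: they follow only if the envelope instruction is carried out as written and, for biased baseline scores, only if the arm reaches the coordinator or the family.

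The concealment claim is overstated. About 27 of 160 allocations known with certainty is a ceiling. It rests on 5:5 blocks, each used up at one site, and an opener with complete knowledge of earlier allocations. The 65% guess rate likewise assumes 5:5 blocks and knowledge of the running difference. Sharing blocks between sites, or having several openers who do not compare notes, would lower both figures.

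The protocol should be corrected, since the instruction is wrong as written and cheap to put right. The documents do not support a conclusion that the trial's randomisation has failed.

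**What to change.** - In Method for Randomization, replace the opening words of the envelope instruction so that it reads: *After the baseline assessment is complete and entered in REDCap, the next envelope is opened.* This agrees with Study Design and Recruitment, and REDCap is already the data system.
- Number the envelopes sequentially and drop the block label from the seal.
- Do not disclose block sizes to site staff. The protocol already prints the size 10, so if that size is kept, staff who know it can still find block ends by counting envelopes. Removing that certainty requires new, varied sizes recorded outside the protocol.
- If sizes are varied, state openly that the lagging-arm guess rate does not fall: about 66% with 6/8/10 and 68% with 4/6/8, against 65% now.
- Delete or soften the statement that the procedure assures concealment.

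The cost is one changed sentence, a softened claim and reprinted envelopes, plus a regenerated list if sizes are varied. A varied list may stop in mid-block, with an imbalance of at most half the largest block. Sample size and analysis are unaffected.

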### **POTENTIAL BENEFITS**

Patients and their parents may derive a sense of personal satisfaction associated with contributing to a study that may ultimately benefit youth at risk for suicide, even though the study may not benefit them individually. In addition, participants found to be at risk of harming themselves or others during the interviews will be assessed by a licensed clinician and referred for treatment if necessary.

Potential benefits to society may be considerable. This study will provide information about the effectiveness of a brief intervention aimed at enhancing referral and linkage of adolescents with previously undetected suicide risk to needed mental health services. If the experimental condition is superior to enhanced care as usual, this could lead to dissemination of better care management strategies than are currently available in the community. Physicians and clinicians who treat youths with undetected suicide risk in ED settings would benefit from such findings. In addition, this study will build the foundation for future work examining the effectiveness of brief interventions that may enhance appropriate mental health-care seeking behavior and improved patient outcomes.

### **POSSIBLE RISKS, DISCOMFORTS, OR INCONVENIENCES**

All of the participants will have been identified as being at risk for suicide. Given this risk, they could also potentially make a suicide attempt and/or complete suicide. However, these risks exist independent of participating in this research.

Risks related to assessments. The main risk associated with the screening and intervention involves a focus on issues that might be upsetting. Talking about self-injury and psychiatric symptoms can potentially be stressful for subjects, particularly for those who are chronically depressed and suicidal. This could in theory cause worsening of suicidal ideation or depressive symptoms, although this has not been consistent with previous experience. So far, we have not encountered any adverse psychological effects among the hundreds of subjects who have participated in our previous research studies of depressed and/or suicidal youth. There is the potential inconvenience of the follow-up interview. However, if risk for harm to self or others is detected in an interview, a risk assessment will be provided by a licensed clinician. Follow-up care will be provided as clinically indicated. Participants may regard this assessment and possible intervention as beneficial, as it provides additional monitoring of participants' wellbeing. In addition, if adolescents are found to be a flight risk or to have significant suicidal risk, the patient will then be treated as per the ED protocol for flight risk. Families will be advised of this as a risk.

Our goal is to audio record all sessions with both intervention (STAT ED) and controls (EUC) once randomized. We will invite all participants allow each session to be audio recorded however If the families do not want to be recorded they will still be enrolled in the study. Such audio recordings will be essential for describing both study conditions, verifying that the two conditions are distinct, assessing intervention fidelity (particularly to Motivational Interviewing), and providing opportunities for interventionists to receive feedback on challenging cases and ways to improve their skills. The audio recording will utilize hospital-approved devices (password protected) and will be regularly downloaded onto a secure server.

Risks of potential breach of confidentiality of study data. The potential for a breach in confidentiality always exists, specifically with written research data and the computerized study database.

### **Risk Minimization**

Procedures for minimizing risks of the interviews: The risk due to interview involves the discussion of potentially upsetting information. Several measures will be taken to protect participants in the study. The ED staff and research staff are trained to assess and monitor the reaction to questioning about sensitive topics. If concerns arise during the initial screening for any participants, licensed clinicians will be contacted and follow-up will occur as clinically indicated. For participants screening positive for suicide

risk, licensed clinicians will conduct a risk assessment and provide follow-up intervention. If risk of harm to self or others exists for which safety cannot be assured at the present time, hospitalization will be pursued.

As for the phone follow-up interviews, parents and adolescents will both need to agree to participate in the follow-up interviews from the same location, as well as to the process to be followed if potential risk is detected. The parents will need to indicate where that location is to the interviewer in the unlikely scenario that police need to be summoned to the home quickly. A member of the research staff will conduct the phone interview and, if potential clinically significant risk for harm to self or others is found, he/she will contact a Cincinnati Children's Hospital or Nationwide Children's Hospital Crisis Team clinician. The clinician will first speak with the parents before beginning the child assessment, remind the parent about the nature of the questions, and ensure that the parent is available at the end of the interview for any safety measures that are needed. The clinician will then conduct a risk assessment of the child over the phone and provide any needed follow-up. We've employed this safety protocol in our ongoing pilot research conducting phone follow-up interviews, and it has proven successful in connecting families to immediate crisis services and addressing immediate safety concerns. As well, feedback on the safety protocol from both staff and participants has been quite positive.

Procedures for minimizing risk due to breach in confidentiality. Subjects will not be promised complete confidentiality during assessments. Information will be shared regarding the limits to confidentiality including situations in which knowledge emerges about the subject being in a dangerous situation: suicidal or homicidal ideation, planned suicide attempt, abuse, or psychosis. In these cases, licensed clinicians will be contacted. Licensed clinicians, as appropriate, will inform the parents of the concerns as well. Research staff may also need to contact child protective services should potential abuse to a child under the age of 18 be reported. This additional limit to confidentiality will be clearly explained to youth and their parents during the consent/assent procedure.

All data gathered from any source during the course of this project will be used solely for research purposes as specified in the specific aims. To protect subject confidentiality, all potential participants will be assigned a four-digit study number when recruited into the study. The four-digit identifier will serve as the only identifier on data forms and within the computer database. All other identifiers such as date of birth, social security number and name will be maintained only in the participant tracking file. The screening record and master list of potential subjects will be stored separately. Information will be kept confidential for the life of the study and destroyed after being maintained in a secure environment for required periods. This file will be destroyed after final follow-up of all patients. These materials will be kept under lock and key with access only by the project coordinator and principal investigator. Consent forms will be maintained separately from study data. An exception to confidentiality is information on child abuse or neglect that is obtained during this research. Such information will be immediately reported to the appropriate authorities. Families will be notified of this exception during the consent process.

CCHMC will be the lead site for this multi-center study. Nationwide Children's will be required to notify the CCHMC PI of any adverse events, protocol deviations, unanticipated problems that have risk/benefit implications, and protocol modifications. Data analysis will be coordinated between the two sites.

### **RISK-BENEFIT ANALYSIS**

The proposed research involves no greater than minimal risk because the study exposes subjects to only small risks associated with interview and breach of confidentiality. It provides potential benefits to participants at current risk to hurt self or others through the provision of a risk assessment by a licensed clinician. It also has the potential to determine the effectiveness of a brief intervention for adolescents with previously undetected suicide risk presenting to pediatric hospital emergency departments. Thus, the likely benefits of this protocol outweigh the potential risks.

### **DURATION**

The project period for this protocol is from September 1, 2012 through December, 2015. It is anticipated that enrollment will begin in January, 2012 and will run through December, 2014. Follow-up calls are expected to be completed from March, 2012 through June, 2015. Data analysis and manuscript preparation will occur from July, 2015 through December, 2015.

### **DATA ANALYSIS METHODS**

#### **Data Storage**

All data will be directly entered into a REDCap Database from both sites. REDCap is a HIPAA-capable web-based data management tool. Exception reports will be run on a regular basis and sent to the sites for corrective action prior to data analysis. In preparation for data analysis, the data will be exported into a SPSS file located on a secured, user access restricted, password protected file.

#### **Variables to be Measured**

Please see uploaded instruments in appendix.

Under the leadership of [name] (Project Statistical Consultant), the team will use a variety of statistical methods to address the primary aims. Preliminary and descriptive analyses will inform subsequent analyses. Graphical representations will help identify aberrations, outliers, and missing data. Skewed data will be transformed or non-parametric approaches used when appropriate. We will start with basic methods, such as the comparison of rates of treatment initiation using chi-squared tests, and then proceed to analyses that may include adjustment for possible confounders and/or effect modifiers. Although we do not anticipate confounding due to an imbalance in covariates because of the RCT design, we will nevertheless test for differences in covariate distribution between study arms. If such imbalance is detected for specific covariates, we will introduce those covariates in the regression models. An indicator variable for site (Cincinnati, Columbus) will be included in all such models. We will use logistic regression models for the binary outcomes associated with initiation in mental health services. For analyses involving the number of follow-up visits, we assume a Poisson distribution. Accordingly, we will use Poisson regression models to assess differences in the number of follow-up visits between groups adjusted for potential confounders, if necessary. In all analyses, we will test for effect modification (interaction) by patient characteristics and study site. In the unlikely event that there is an interaction between study arm and study site, we will report site-specific results. We will use regression diagnostics to check our models for co-linearity and influential observations, using residual plots and associated quantitative methods.

Our primary analyses will compare STAT-ED and EUC using ITT analyses. Analysis by ITT requires that outcomes will be analyzed by randomization without regard to subject adherence to the study protocol. We will perform analyses to characterize participants who leave the study early relative to others.

Hypothesis 1: STAT-ED will be superior to EUC in improving treatment initiation and overall treatment attendance. We will compare the rate of mental health treatment initiation in the STATED and EUC groups using the standard chi-square test of proportions. We plan to calculate effect sizes and confidence intervals in addition to simple tests of significance. As mentioned earlier, logistic regression models for adjustment will be used in the event of imbalance in any important covariates. We will compute the number needed to treat to benefit (NNTB) as an additional measure of the clinical significance of the impact of the STAT-ED intervention on treatment initiation rates relative to EUC. The analysis of overall number of treatment sessions attended by participants in each arm will use a likelihood ratio test based on the Poisson distribution. Similar to the analysis of treatment initiation, Poisson regression models will be used if covariate adjustment is necessary or for assessment of effect modification.

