## **PURPOSE**

This two-site study tests the effectiveness of a brief treatment engagement intervention termed Suicidal Teens Accessing Treatment after an ED Visit (STAT-ED) for adolescents seeking treatment in the ED for non-psychiatric concerns but identified via systematic screening as being at risk for suicide. In this 3-year proposal, investigators from two institutions (Cincinnati Children’s Hospital Medical Center [CCHMC] and Nationwide Children’s Hospital [NCH]) will recruit and randomize 160 adolescents (80 per site) to (a) the STAT-ED intervention or (b) enhanced usual care (EUC) as a comparison condition. EUC consists of a brief consultation and a mental health referral. The STAT-ED intervention targets family engagement, problem solving, motivational interviewing, assistance with referral and limited case management during the transition from the ED to outpatient care with the goal of maximizing the initiation of mental health treatment and aftercare among youth screening positive for previously unrecognized suicide risk.

The primary aim of this study is to test the following two hypotheses:

1. Adolescents receiving the STAT-ED intervention will have a significantly higher rate of initiating mental health treatment and will attend more mental health treatment sessions in the two months after the ED visit compared with adolescents in the EUC condition.
2. STAT-ED will be superior to EUC in reducing suicidal ideation and depression symptoms at two months and six months.

Secondary aims are exploratory and designed primarily to provide estimates of effect size for future larger-scale investigations:

1. Determine whether the effectiveness of the STAT-ED intervention differs by age, gender, or ethnicity.
2. Evaluate predictors and mediators of mental health treatment engagement. We hypothesize that mental health treatment engagement in both arms will be predicted by higher clinical suicide severity, lower family barriers to treatment, and lower service access barriers. High scores in the action stage of change will predict successful mental health treatment engagement, in general, but particularly for those enrolled in STAT-ED.

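### Adjustment for covariates other than site depends on a baseline test between arms, so chance decides the adjusted model, and the plan does not say which result leads

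*Protocol*

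**What the plan says.** The statistical text in the Protocol, under Variables to be Measured, does not expect confounding because the trial is randomised. It continues: "we will nevertheless test for differences in covariate distribution between study arms". The consequence follows: "If such imbalance is detected for specific covariates, we will introduce those covariates in the regression models".

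The Hypothesis 1 paragraph applies the rule to each engagement outcome. For initiation, a chi-square test of proportions is the planned comparison, and "logistic regression models for adjustment will be used in the event of imbalance in any important covariates". For the number of sessions, the planned test is a Poisson likelihood ratio test, and "Poisson regression models will be used if covariate adjustment is necessary or for assessment of effect modification". No threshold for imbalance is given.

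Site is treated differently: "An indicator variable for site (Cincinnati, Columbus) will be included in all such models". Site is thus fixed in the regressions but is not part of the chi-square test.

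On interactions: "In all analyses, we will test for effect modification (interaction) by patient characteristics and study site". Then: "In the unlikely event that there is an interaction between study arm and study site, we will report site-specific results".

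The secondary aims under Purpose hypothesise that engagement in both arms will be "predicted by higher clinical suicide severity, lower family barriers to treatment, and lower service access barriers".

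**The concern.** Allocation is by computer-generated blocks with sealed envelopes (Method for Randomization). If that works, any baseline difference between arms is a chance difference, and a test for it gives no information about confounding. Used as a gate, the test selects covariates by how far they happen to differ and not by how well they predict the outcome. A strong predictor that happens to balance is left out, and an irrelevant variable that happens to differ goes in.

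Two things are left open as a result. First, when a covariate is flagged there are two results for initiation, the chi-square and the adjusted model, with no statement of which is the trial's answer. Second, a site interaction triggers site-specific reporting, with no statement that the pooled effect remains the main result. Precision is also given up, because the Protocol's own candidate predictors are used only if they happen to be imbalanced.

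**Working it through.** **Inputs from the Protocol (Sample Size Justification; Study Sample).** Two-sided alpha 0.05, power 80%, initiation 50% under EUC, a 50% relative improvement (so 75% under STAT-ED), 80 per arm, and 80 per site (so about 40 per arm per site).

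**Assumptions, because the Protocol gives no figure.** Threshold and number of baseline tests, independence of the covariates, strength of the prognostic covariates, and the correlation between baseline and follow-up scores.

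**1. The plan's own figure.** With d = 0.25 and mean rate 0.625:

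n = [1.96·√(2·0.625·0.375) + 0.842·√(0.25 + 0.1875)]² / 0.25² = 57.7, or 58 per arm.

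Continuity correction: (57.7/4)·[1 + √(1 + 4/(57.7·0.25))]² = 65.4, or 66 per arm. This matches the stated 66.

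**2. How often the gate opens.** With k independent covariates at 5%, P(at least one flagged) = 1 − 0.95^k:

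| k | P |
|---|---|
| 3 | 14% |
| 5 | 23% |
| 10 | 40% |
| 20 | 64% |

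At a 10% threshold with k = 10 it is 1 − 0.90^10 = 65%.

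**3. What the gate does to error and power for initiation.** Simulation with 6,000 trials per scenario, 80 per arm and 8 independent baseline covariates, of which 3 are prognostic with an assumed log odds ratio per SD of 0.3, 0.5 or 0.7. Marginal rates were 50% against 75% under the alternative and 50% in both arms under the null. The gated rule uses the chi-square unless something is flagged, and otherwise a logistic model with site and the flagged covariates.

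| | 0.3 | 0.5 | 0.7 |
|---|---|---|---|
| Type I error, gated rule | 4.5% | 4.4% | 4.4% |
| Type I error, 3 predictors plus site pre-specified | 5.3% | 4.8% | 5.0% |
| Power, unadjusted chi-square | 90.8% | 91.0% | 90.8% |
| Power, gated rule | 90.5% | 91.2% | 90.9% |
| Power, 3 predictors plus site pre-specified | 92.0% | 94.2% | 95.7% |

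Pre-specified minus gated: 1.5, 3.0 and 4.8 points.

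**4. Ideation and depression.** Adjusting a follow-up score for its baseline value multiplies residual variance by 1 − r². For r = 0.3 the cut is 0.09, or 9%. For r = 0.7 it is 0.49, or 49%. The Protocol gives no r.

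**5. The site rule.** If there is no interaction, a 5% test still fires 1 time in 20. If the effect is 50% to 75% at one site and absent at the other, the difference in log odds ratios is ln 3 = 1.099. Its standard error is √(3/(40·0.25) + 1/(40·0.1875)) = 0.658, so power is Φ(1.099/0.658 − 1.96) ≈ 39%.

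A single site with 40 per arm, for 50% against 75%, has power Φ[(0.25·√40 − 1.342)/0.661] = Φ(0.36) = 64%. With continuity correction (0.25 − 1/40 in place of 0.25) it is Φ(0.12) = 55%. The same uncorrected formula at 80 per arm gives Φ(1.35) = 91%.

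**The case against.** The strongest reply is that the primary comparison is fixed. The chi-square for initiation is named without condition, the text says it will begin with basic methods, and the sample size rests on that test. This stands: chance does not choose the headline test. It decides whether an adjusted model is added and what is in it. What remains open is which result leads.

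Five further points limit the finding.

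- A reader might infer that choosing covariates after seeing the arms inflates the false-positive rate. The simulation does not support that when the rule is followed mechanically (4.4% to 4.5%). The remaining risk is an analyst choosing between two results after seeing both.
- A reader might infer that a site interaction replaces the pooled result with two half-size comparisons. The text says only that site-specific results will be reported. The 64% and 55% figures matter only if those results were relied on.
- A reader might apply the anticipated retention of over 85% to the site halves and quote still lower power. For the primary aim, Sample Size Justification says that intention-to-treat keeps all 160, so 40 per arm per site is the right basis.
- The predictors are hypothesised, within aims described as exploratory. They are expected, not known, to be prognostic.
- Adjustment for initiation is limited to covariates called important, and a covariate list can be left to an SAP. That covers the missing list but not the trigger. An SAP that follows the Protocol inherits the baseline test, and one that pre-specifies covariates contradicts it.

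**Conclusion.** The point holds in a limited form. For covariates other than site, the Protocol states a data-driven adjustment rule that is inferior to pre-specification. It leaves two orders of precedence unstated: unadjusted against adjusted, and pooled against site-specific.

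For initiation the loss is modest, about 1.5 to 5 points of power against about 91% for the unadjusted test. That range rests on the assumed three prognostic covariates and their strengths. For ideation and depression the gain from baseline adjustment could be small or large (9% to 49% of residual variance for r from 0.3 to 0.7), and the Protocol gives nothing to narrow it. The 14% to 64% chance of triggering adjustment rests on an assumed 5% threshold and independent covariates.

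The rule does not invalidate the planned chi-square. It should still be corrected, because the change is only to wording and it removes any choice between results after the data are seen.

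**What to change.** 1. Delete baseline testing as the trigger for adjustment, both under Variables to be Measured and in the Hypothesis 1 paragraph. Baseline characteristics can still be tabulated by arm.
2. Pre-specify a short covariate list: site and the predictors hypothesised under Purpose (suicide severity, family barriers, service access barriers) as measured at baseline. For ideation and depression, add the baseline value of the scale.
3. Name one lead analysis for each outcome and make the other supporting. For initiation the pair is the adjusted logistic model and the unadjusted chi-square.
4. State that the pooled, site-adjusted effect is the main result whatever the interaction test shows, with site-specific estimates given as supportive.

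The cost is slightly more analysis work and a few model terms, with no change to the sample size. One point needs confirming. That these covariates are collected at baseline is inferred from the aims under Purpose and the baseline assessments described under Procedure, because the instrument appendix is not shown.
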